#### Data collection

2.2.8

Data quality control will be conducted by a combination of centralized (remote) and on-site monitoring, according to each procedures standardized protocols. Centralized monitoring will be conducted by the coordinating investigator, the coordinating office, and the data center conducting the data collection. The data center will verify the progress of the clinical trial, the visit of each patient, protocol compliance, and the occurrence of adverse events. A centralized monitoring report will be created by the data center and submitted to the coordinating investigator, who will ensure that the study is conducted properly and safely based on the centralized monitoring report and will take appropriate measures when necessary.

The on-site monitoring will ensure that the study is conducted in compliance with the protocol and good clinical practice guidelines, as well as assess the electronic case report forms. The data manager will check for inconsistencies. The quality assurance auditor will assess the quality of the study independently according to the quality assurance plan. Moreover, the auditor will assess that the study is conducted in compliance with the protocol and good clinical practice guidelines.

#### Sample size calculation

2.2.9

Assuming a null hypothesis of a response rate of ≤5% and an alternative hypothesis of 25%, a minimum of 26 patients are required to achieve a 5% two-sided type I error and 80% power based on the exact binomial distribution. A target sample size of 30 was set to account for an expected patient dropout of 10%.

### Statistical analysis

2.3

Statistical analyses and reporting will be conducted in accordance with the Consolidated Standards of Reporting Trials guidelines, with the primary analyses based on the intent-to-treat principle without imputing any missing observations. All efficacy analyses will be based primarily on the full dataset, which includes all patients who have received at least 1e dose of nivolumab and were in accordance with the study protocol. Safety analysis will be conducted using data from the safety analysis population. For baseline variables, summary statistics will be performed using frequencies and proportions for categorical data and means and standard deviations for continuous variables.

The primary endpoint for efficacy will the proportion of responders, considering a response threshold of 5% (H_0_, null hypothesis) and an expected response rate of 25% (H_1_, alternative hypothesis). The 95% confidence intervals will be calculated according to the binomial distribution of the response rate. The confidence interval limits will be assessed against the response threshold.

Subgroup analysis will be performed to evaluate safety and efficacy depending on the tumor subtype. All statistical analyses will be performed using SAS software version 9.4 (SAS Institute). All statistical analyses will be described in detail in the statistical analysis plan, which will be fixed prior to database lock.

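### The primary efficacy analysis is called intent-to-treat, but its population carries a protocol-accordance condition that is ambiguous and, on its natural reading, per-protocol

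*Protocol article*

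**What the plan says.** Two consecutive sentences in section 2.3 (Statistical analysis) of the protocol article define the primary analysis. The first describes the analysis "with the primary analyses based on the intent-to-treat principle without imputing any missing observations". The second rests all efficacy analyses primarily on what it calls the full dataset, "which includes all patients who have received at least 1e dose of nivolumab and were in accordance with the study protocol".

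The same section sets the success criterion. The 95% binomial confidence interval for the response rate is computed, and "The confidence interval limits will be assessed against the response threshold", the threshold being 5%. Section 2.2.9 (Sample size calculation) says that "a minimum of 26 patients are required to achieve a 5% two-sided type I error and 80% power based on the exact binomial distribution", for 5% against 25%. It then sets a target of 30 to allow for 10% dropout.

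The article does not say what being in accordance with the protocol means, who decides it, or when. Section 2.3 leaves analysis detail to a statistical analysis plan to be fixed before database lock.

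**The concern.** A condition on adherence to the protocol is what separates a per-protocol set from an intent-to-treat set, so the two sentences cannot both govern the primary analysis as they stand.

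The trial is open-label and single-arm, with imaging every two cycles. Responses accumulate in plain view, and section 2.2.8 (Data collection) has protocol compliance verified while the trial runs. If the condition covers conduct after the first dose, a treated patient could be removed once the response is known. That matters because the primary conclusion turns on a small number of responders, and the Discussion says the study could lead to regulatory approval.

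The instruction not to impute missing observations adds a second route to a smaller denominator: a treated patient with no evaluable response might simply be left out.

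**Working it through.** **Inputs.** Null rate 5%, alternative 25%, two-sided 5% (2.5% in the upper tail), 80% power, minimum 26, target 30, dropout 10%: all from section 2.2.9. Success when the lower 95% limit exceeds 5%: section 2.3. Assumption: the limits are exact (Clopper-Pearson), because section 2.2.9 names the exact binomial distribution and section 2.3 says only that the interval is binomial.

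**Formulas.** The exact lower limit L for x responders in n solves P(X ≥ x | n, L) = 0.025. It exceeds 5% when P(X ≥ x | n, 0.05) < 0.025. The cut-off r is the smallest x meeting this, and power is P(X ≥ r | n, 0.25).

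**Step 1: reproduce the plan's figure.** At n = 26, P(X ≥ 4 | 0.05) = 0.0387, which is too large, and P(X ≥ 5 | 0.05) = 0.0085. So r = 5 and power is 81.6%. Power is 71.7%, 75.3% and 78.6% at n = 23, 24 and 25, and it stays at or above 80% from 26 on (checked to 35). The stated 26 is reproduced. For dropout, 26/0.90 = 28.9, so 29, which the target of 30 covers.

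**Step 2: the cut-off.** It is 5 for every n from 23 to 33, and 4 at n = 22. At n = 30 the upper-tail type I error is 0.0156 and power is 90.2%.

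**Step 3: effect of exclusions.**

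| Responders / analysed | Rate | Exact 95% CI | Lower limit above 5%? |
|---|---|---|---|
| 5/30 | 16.7% | 5.6% to 34.7% | yes |
| 4/29 (one responder excluded from 5/30) | 13.8% | 3.9% to 31.7% | no |
| 5/27 (three non-responders excluded from 5/30) | 18.5% | 6.3% to 38.1% | yes |
| 4/30 | 13.3% | 3.8% to 30.7% | no |
| 4/23 (seven non-responders excluded from 4/30) | 17.4% | 4.95% to 38.8% | no |
| 4/22 (eight non-responders excluded from 4/30) | 18.2% | 5.2% to 40.3% | yes |

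**Step 4: error rates.**
- If up to 7 non-responders could be dropped selectively from 30, the cut-off stays at 5 and the upper-tail error stays at 0.0156.
- If 8 or more could be dropped, 4 responders would be enough, and the worst case is P(X ≥ 4 | 30, 0.05) = 0.0608.
- Eight of 30 is 26.7%. The planned dropout of 10% is 3 patients.
- If only 26 patients were treated, reaching 22 would take 4 exclusions (4/26 = 15.4%), with a worst case of P(X ≥ 4 | 26, 0.05) = 0.0387.

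**Step 5: power.** If exclusions are unrelated to response, the true rate among those left is still 25%. Power then falls from 90.2% at n = 30 to 84.2% at n = 27, because the cut-off does not move.

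**Step 6: how often the result is borderline.** P(X = 5 | n = 30) is 10.5% at a true rate of 25% and 17.2% at 20%.

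**The case against.** **The phrase may be innocent.** The sentence is loosely edited, calls the set the full dataset, and does not use the term per-protocol. It could mean only that patients were enrolled in accordance with the protocol. Excluding ineligible patients on facts fixed before treatment is a much milder departure from intent-to-treat. This stands as a possible reading. It does not rescue the text, which does not say so and equally permits exclusions for later conduct.

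**Outcome-aware exclusion is not shown.** A reader might infer that patients will be removed at someone's discretion with responses in hand, for missed scans or dosing deviations, say. The article does not support that. It lists no such grounds, and it does not link compliance monitoring in section 2.2.8 to membership of the analysis set. The statistical analysis plan may define the condition narrowly. What can be said is that the wording allows such exclusions.

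**A false claim of efficacy is not a realistic outcome.** A reader might also infer that exclusions could readily turn failure into success. With 30 treated, the figures do not support this: 4/23 still fails, and eight non-responders would have to go. The easy reversal, losing one responder from 5/30, works against the drug. The 10.5% and 17.2% are chances of landing on exactly five responders. They are not chances of a reversal, which also requires a responder to be excluded. All of this stands and limits the severity.

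**The detail belongs in the analysis plan.** This would answer a silent article. Here the article states a population, and states it in conflict with its own principle.

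**Conclusion.** The conflict is real and should be fixed before the data are analysed. Section 2.3 names one principle and writes a population that, on its natural reading, follows another.

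The realistic consequences are three: a modestly inflated response rate if non-responders are dropped (16.7% to 18.5% in the example), some loss of power if exclusions are unrelated to response (90.2% to 84.2% for three fewer patients), and a possible lost success if a responder is excluded at the cut-off of five. Type I error is not materially inflated at the exclusion rates the plan expects. This is therefore a should-fix point and does not undermine the design.

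The figures assume exact limits. With a Wilson interval the cut-off at 26 to 30 patients would be 4 (4/30 has lower limit 5.3%). With a Wald interval 5/30 would fail (lower limit 3.3%). The conflict between the two sentences does not depend on the interval method.

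**What to change.** In section 2.3 and in the statistical analysis plan:

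1. Delete the condition on accordance with the protocol, and define the primary efficacy set as all enrolled patients who received at least one dose of nivolumab.
2. State that treated patients without an evaluable response stay in the denominator as non-responders. Otherwise the rule against imputation leaves another route to a smaller denominator.
3. Describe the set as all-treated. Enrolled patients who never receive a dose are outside it, so intent-to-treat is not the right label.
4. Report a protocol-compliant set, if wanted, only as a labelled sensitivity analysis.

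The cost is a few sentences and no extra patients. The observed response rate may be slightly lower. With 30 treated the criterion remains at least 5 responders, with upper-tail type I error 0.0156 and power 90.2%.

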### Confidentiality

2.4

All study-related information will be stored securely on-site and identified by a coded number only to ensure participant confidentiality. All records that contain names or other personal identifiers will be stored separately from study records identified by code number. All local databases will be secured with password-protected access systems. Data generated by this trial will be considered confidential by the investigators, except for data to be included in publications.

### Patient and public involvement

2.5

No patient involved.

## Discussion

3

This is a single-arm clinical trial that involves the use of nivolumab in Japanese patients with metastatic cSCC or other rare malignant cutaneous epithelial tumors. The rationale of this study relies on the several previous clinical and basic evidences (Table 1). In a phase I study assessing the usefulness of the PD-1 inhibitor cemiplimab in patients with metastatic and locally advanced cSCC, an overall response rate of 50% was reported. In a phase II study, the overall response rate was 47.5% (28/59 cases), including 4 cases of complete remission. By integrating the results of these 2 studies, the response rate of metastatic cSCC to cemiplimab was 46.7% (35/75 cases).^[40]^ The clinical benefit of anti-PD-1 antibodies for rare malignant cutaneous epithelial tumors have also been reported by several case reports. Successful treatment with nivolumab of advanced BCC patients refractory to Hedgehog signaling inhibitors has been reported.^[41]^ Another case report demonstrated that treatment with pembrolizumab resulted in a partial response in a patient with cutaneous apocrine carcinoma.^[42]^ The tumor mutation burden has been associated with the neoantigen burden and response to anti-PD-1 treatment in melanoma.^[43]^ Importantly, cSCCs are reported to have a high mutation burden among various cancer types.^[44,45]^ Furthermore, some EMPD cases demonstrated a similar tumor mutation burden as that in SCC cases.^[46]^ Based on these clinical and biological observations, we hypothesize that nivolumab will also show a clinical benefit in multiple malignant cutaneous epithelial tumor types, regardless of any biological and pathological differences.

**Table 1 T1:**

Reported anti-PD-1/-L1 therapies for advanced epithelial skin malignancies.

The fact that PD-1 inhibitors have gained regulatory approval for use in cSCC in the U.S. but not in Japan is mainly attributed to differences in the incidence of metastatic cSCCs. The incidence of cSCC in Caucasian populations is reported to be 17 to 360 per 100,000 cases, which is 5.8 to 138 times higher than that in Asian populations (2.6–2.9 per 100,000 cases).^[47]^ In a survey of the prevalence of advanced NMSCs in Japan, the annual reported number of advanced cSCC patients was 323.5.^[48]^ Nevertheless, the incidence of metastatic cSCC is increasing. The 5-year OS rate of cSCC patients treated with conventional cytotoxic chemotherapy is 26% to 29%, suggesting that metastatic cSCCs are also life-threatening among Japanese patients, and that the establishment of novel therapeutic approaches remains an unmet medical need.^[49]^ To address this issue, we designed this clinical trial involving Japanese patients with metastatic cSCC. We decided to also include patients with other metastatic adnexal tumors to potentially expand the range of cancer types treated with PD-1 inhibitors. Because these tumor types are extremely rare, well-controlled clinical trials involving patients with such tumors are unlikely to be conducted.

This study design has several limitations, most of which are because of the rarity of the tumor types involved. The first, number of patients enrolled will be low, and the cancer type varies among the study participants. The second, differences and heterogeneity in the response to nivolumab among the study participants are expected, due to potential differential sensitivity of the different cancer types to immunotherapy. Nevertheless, the present study could lead to the regulatory approval of nivolumab for use in Japanese patients with malignant cutaneous epithelial tumors, the treatment of which remains an unmet clinical need.

### Trial status

3.1

The trial is currently actively recruiting patients. Completion of patient recruitment is expected for the beginning of 2021.
